## Abstract

**Background:**

Presentations to hospital of older people receiving family care at home incur substantial costs for patients, families, and the health care system, yet there can be positive carer outcomes when systematically assessing/addressing their support needs, and reductions in older people’s returns to hospital attributed to appropriate discharge planning. This study will trial the Further Enabling Care at Home program, a 2-week telephone outreach initiative for family carers of older people returning home from hospital. Hypotheses are that the program will (a) better prepare families to sustain their caregiving role and (b) reduce patients' re-presentations/readmissions to hospital, and/or their length of stay; also that reduced health system costs attributable to the program will outweigh costs of its implementation.

**Methods/Design:**

In this randomised controlled trial, family carers of older patients aged 70+ discharged from a Medical Assessment Unit in a Western Australian tertiary hospital, plus the patients themselves, will be recruited at discharge (*N* = 180 dyads). Carers will be randomly assigned (block allocation, assessors blinded) to receive usual care (control) or the new program (intervention). The primary outcome is the carer’s self-reported preparedness for caregiving (Preparedness for Caregiving Scale administered within 4 days of discharge, 2–3 weeks post-discharge, 6 weeks post-discharge). To detect a clinically meaningful change of two points with 80 % power, 126 carers need to complete the study. Patients’ returns to hospital and subsequent length of stay will be ascertained for a minimum of 3 months after the index admission. Regression analyses will be used to determine differences in carer and patient outcomes over time associated with the group (intervention or control). Data will be analysed using an Intention to Treat approach. A qualitative exploration will examine patients’ and their family carers’ experiences of the new program (interviews) and explore the hospital staff’s perceptions (focus groups). Process evaluation will identify barriers to, and facilitators of, program implementation. A comprehensive economic evaluation will determine cost consequences.

**Discussion:**

This study investigates a novel approach to identifying and addressing family carers’ needs following discharge from hospital of the older person receiving care. If successful, the program has potential to be incorporated into routine post-discharge support.

**Trial registration:**

Australian and New Zealand Clinical Trial Registry: ACTRN12614001174673.

## Background

This study is being conducted in metropolitan Western Australia (WA), where increasing numbers of older people are experiencing multiple chronic health conditions, disability, and high level health care utilization [1]. This situation parallels that in other western countries in which life expectancy is increasing [2] and, together with predictions of health workforce shortages [3], highlights the need to increase support for family-based home care within the community [4]. There were close to 350,000 informal primary carers of older people in Australia in 2009, saving an estimated $40 billion in service provision costs each year [5] but poor health has long been a recognised family caregiver outcome, with support needed to help carers to sustain their caregiving role [6].

For older people receiving care and in poor health, readmissions to hospital are potentially distressing and costly, yet sometimes avoidable with high quality discharge planning [7]. A key component of effective discharge planning is to closely involve the family carers [8]. However, in a recent study investigating returns to hospital after discharge from a short stay (<72 h) Medical Assessment Unit (MAU), communication issues at the time of discharge presented a significant challenge [9]. There was limited opportunity for the staff to liaise with family carers in the time available prior to discharge. In particular, there was insufficient time allocated to assess carers’ needs and communicate plans to them for addressing likely future health crises for patients [9].

In parallel work in community palliative care in the United Kingdom, a need for a systematic and effective carer needs assessment process was identified. The Carer Support Needs Assessment Tool (CSNAT) was developed following extensive reviews of the literature [10–12], and from interviews with bereaved carers [13]. The tool was subsequently validated using a sample of 225 current carers [14]. The CSNAT is a brief tool, yet covers all identified support need areas. Each item represents a core carer support domain in home care. The items fall into two sets: those that enable the carer to care for the patient at home and those that enable direct support for the carer [13]. The CSNAT has recently been used in a Western Australian study in palliative home care; it was reported to be practical and useful; to prompt carers to consider their own needs rather than just those of the patient; to validate, reassure, and empower carers; and to help carers access the support that they need [15].

The aim of this study is to determine how implementing an evidence-based, systematic, and targeted support program for family carers of older patients - immediately after the patient’s discharge from a metropolitan Western Australian hospital’s MAU - impacts upon these carers; the patients for whom they provide care; and costs to WA Health, the local health care system. The program being evaluated is termed the Further Enabling Care at Home (FECH) program, and it uses the CSNAT to identify and prioritise family carers’ support needs that are subsequently addressed. The study has three hypotheses:H1: That the enhanced support of family carers facilitated by the FECH program will prepare families to sustain their caregiving role better than usual care.H2: That, because family carer roles are better supported, implementation of this program will reduce (a) patients’ re-presentations and readmissions to hospital within 3 months of discharge, and (b) length of hospital stay when readmissions do occur.H3: That reduced costs to WA Health will outweigh costs of implementing the program.

Study objectives are to:Compare family carer preparedness to care between those included in the FECH program and those receiving usual care.Compare patient outcomes from the FECH program versus those from usual care in terms of re-presentations to Emergency Departments (EDs), readmissions to hospital within the months (at least 3) following the index separation date – also Length of Stay (LoS) if readmission does eventuate.Document costs of a suitably qualified nurse (FECH nurse) implementing the program to inform the economic evaluation and determine a sustainable full time FECH nurse ‘caseload’.Compare costs of re-presentations to EDs, hospital readmissions, and LoS between the intervention group (FECH program) and the control group (usual care).Estimate overall cost effectiveness for the local health system from FECH program implementation during the study period.Explore and describe family carers’ perceptions of how the FECH program impacts upon caregiving sustainability plus any other outcomes for them; also how it might be refined to (a) minimise any negative outcomes, (b) enhance those that are positive, and (c) (further) enhance caregiving sustainability.Explore and describe patients’ perceptions of how the FECH program impacts upon them and how it might be refined to ensure the best possible outcomes (for them).Use process evaluation and obtain perspectives of MAU health care professionals to determine how the FECH program’s implementation might be improved.Refine the program from study recommendations and develop a plan to embed it into practice in the study setting and other similar health services.Develop a plan for testing the FECH program in other health settings – should it be shown to have cost benefits and no negative patient/carer outcomes when implemented in the MAU.

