### Statistical analysis

Data analyses will be performed using the IBM SPSS statistical software package [31]. A p-value of <0.05 will be taken to indicate a statistically significant result in all tests.

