#### Patient outcomes

Patient outcomes will be compared between groups using t-tests or regression models. For example, the total length of hospital stay will be calculated and compared between groups using a *t*-test (after log-transformation of the data if indicated). Number of re-admissions to hospital or presentations to ED will be compared using the same method. A regression model will be used to take into account potentially confounding variables (if relevant). The association between change in preparedness and change in health care utilisation will be evaluated using carer outcomes linked to the administrative data.

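### Hypothesis 2(b) concerns length of stay given readmission, but the only named analysis compares total length of stay; the two should be aligned on total days per randomised patient

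*Protocol article*

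**What the plan says.** The hypotheses in the Background of the protocol article split H2 in two. H2(a) expects fewer "re-presentations and readmissions to hospital within 3 months of discharge". H2(b) expects a shorter "length of hospital stay when readmissions do occur". The second study objective, in the same section, carries the same condition: "also Length of Stay (LoS) if readmission does eventuate".

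Under Statistical analysis, Patient outcomes, the general rule is "Patient outcomes will be compared between groups using t-tests or regression models". One length-of-stay analysis is then given as an example: "the total length of hospital stay will be calculated and compared between groups", by t-test, "after log-transformation of the data if indicated". Counts of readmissions and emergency presentations are to be compared by the same method. The section does not say whether patients with no readmission enter the total as zero, and it names no separate analysis of stay among readmitted patients. The abstract states that "Data will be analysed using an Intention to Treat approach".

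**The concern.** The hypothesis and the named analysis address different quantities. H2(b) asks how long a stay is once a patient is back in hospital. Total stay per patient also depends on how often patients come back. If the program prevented readmissions and shortened nothing, total stay would still fall, and a reader could take that as confirmation of H2(b).

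Analysing the hypothesis literally, among readmitted patients only, brings a different problem. Readmission happens after randomisation, and H2(a) says the program will alter it. If the program works in that way, the readmitted patients in the two arms are different selections of patients, and a difference in their mean stay mixes any real shortening with that selection. What is at stake is what the trial may conclude on one part of a formal hypothesis.

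**Working it through.** The plan gives no figure to reproduce here: it states no readmission rate, stay length or variance for patient outcomes. The check is therefore a reading of the text plus an illustration in which all rates and stay lengths are assumed.

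**Inputs.** From the protocol: 180 dyads in two arms filled at about the same rate, so about 90 per arm; significance level 0.05. Assumed: control readmission p_C of 30% to 50%; program readmission p_T lower by 5 to 15 percentage points; at most one readmission per patient; the program adds no readmissions; readmissions that are not prevented average 6 days; prevented ones average m = 3, 6 or 9 days; no stay changes in length.

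**Formulas.**
- Mean stay among the readmitted, control: [p_T × 6 + (p_C − p_T) × m] / p_C. Program: 6.
- Total stay per randomised patient, control: p_T × 6 + (p_C − p_T) × m. Program: p_T × 6.

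**Worked case, p_C = 0.40, p_T = 0.30, m = 3.** Control total = 0.30 × 6 + 0.10 × 3 = 2.10 days; control mean among the readmitted = 2.10 / 0.40 = 5.25 days. Program total = 0.30 × 6 = 1.80 days; program mean among the readmitted = 6.00 days.

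| m (days) | Readmitted only: control vs program | Difference | Total per patient: control vs program | Difference |
|---|---|---|---|---|
| 3 | 5.25 vs 6.00 | +0.75 | 2.10 vs 1.80 | −0.30 |
| 6 | 6.00 vs 6.00 | 0 | 2.40 vs 1.80 | −0.60 |
| 9 | 6.75 vs 6.00 | −0.75 | 2.70 vs 1.80 | −0.90 |

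Over the whole assumed grid, the difference among the readmitted runs from −1.5 to +1.5 days and the difference in total from −0.15 to −1.35 days, although no individual stay has been altered.

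**Simulation.** 90 per arm, 3,000 runs, readmission 40% vs 25%, log-normal stays with log-scale SD 0.8, and again no stay altered:
- A t-test on log stay among the readmitted gave p < 0.05 in about 39%, 20% and 5% of runs when prevented stays averaged 2, 3 and 6 days. With 40% readmitted in both arms it did so in about 5%.
- A t-test on untransformed total stay over all patients gave p < 0.05 in about 9%, 15% and 31% of runs in the same three settings. Those rejections reflect a true reduction in total days, but none of it comes from shorter stays.

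**The log-transformation.** The logarithm of 0 is undefined. At 40% and 30% readmission, 0.60 × 90 = 54 and 0.70 × 90 = 63 patients would have a total of 0. If the transformation led to these being dropped, the comparison would rest on 36 and 27 readmitted patients. The total comparison would then have become the restricted one without anyone having decided so.

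**The case against.** The strongest reply is that the plan commits to no faulty analysis. Total stay is offered as an example under a general rule, this is a condensed article, and a full analysis plan may list more. If the total is taken over all randomised patients, which is the natural reading given the intention-to-treat statement, the named comparison is sound and the selection problem arises nowhere in the text. The conditional wording may also be loose description: after the index discharge, a hospital stay exists only if there is a readmission. The abstract and the objective on costs refer to length of stay without a strict condition.

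Much of this stands. It rules out one stronger reading that a reader might draw, that H2(b) is left wholly untested or can never be answered. The text excludes no further analysis, and principal-stratum methods could address the conditional question under added assumptions. It does not remove the discrepancy. H2(b) and the objective are both worded conditionally, and the one analysis printed is not. If a conditional analysis is meant, it lacks the protection of randomisation; if it is not meant, the hypothesis is misworded.

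A second tempting reading is that preventable stays are the short ones, so that a beneficial program would appear to lengthen stays and H2(b) would look refuted. Nothing in the documents says preventable stays are shorter, and the table shows the bias can go either way or vanish. Even a favourable invented case does not get that far. Take 40 control readmissions, half of 2 days and half of 8 (mean 5.0), against 30 in the program arm after ten 2-day stays are prevented (mean (10 × 2 + 20 × 8) / 30 = 6.0). The difference is 1.0 day with a standard error of about 0.71, p about 0.17, which does not meet the plan's own criterion: "A p-value of <0.05 will be taken to indicate a statistically significant result in all tests".

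**Conclusion.** The concern holds as a mismatch between a stated hypothesis and the analysis named for it. A fall in total length of stay would not by itself support H2(b), and a comparison confined to readmitted patients would condition on an event that H2(a) expects the program to change. The second statement depends on the program affecting readmission; if readmission is unaffected, that selection does not arise. The direction of any bias is unknown, and so is its size; the figures above show what is possible under assumed inputs and are not estimates for this trial.

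The consequence is limited. Length of stay is a patient outcome; the primary outcome is carer preparedness, which also sets the sample size. The cost comparison counts inpatient costs by arm and does not rely on stay given readmission. The change is worth making because it settles what may be concluded on H2(b) and keeps that conclusion on the randomised groups.

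**What to change.** 1. Restate H2(b) and the second objective as total days in hospital within 3 months of index separation, per randomised patient, counting 0 for those not readmitted. The fixed window matters because linked data will run for about 9 months overall, so earlier recruits have more follow-up than later ones.
2. In the Patient outcomes analysis, state that the total is over all randomised patients and that zeros are kept. A plain log-transformation is undefined at 0 and must not be allowed to drop them. State alongside this how patients who die within the window are counted; dates of death are already to be collected.
3. Report length of stay among readmitted patients descriptively by arm, or with an explicit caveat that it is not a randomised comparison.

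The cost is the rewording of one hypothesis and one objective, plus a few sentences of analysis text. The linked records already contain admission and separation dates, so no new data are needed. The small downside is that total days do not separate fewer stays from shorter ones; the readmission counts and the descriptive table give the reader that breakdown.

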### Patient outcomes and data collection

Quantitative patient outcome data will address Western Australian health care system utilisation and will be obtained through linked administrative health data provided via the WA Data Linkage System (WADLS) [28]. These Data Linkage Unit (DLU) data will capture reason for service and mode of transport plus: date of service, symptom/presenting problem, and triage code (ED presentation); admission and separation dates, primary diagnosis code, co-diagnosis code, and diagnosis related group (hospitalisation data). In addition, to account for time at risk, and to capture deaths resulting from acute events during the study follow-up period, date and cause of death will be collected.

The data retrieved from data linkage will cover the time period from the date of the index separation of the patient whose carer is the first to be recruited to the study until 3 months after the index separation of the patient whose carer is the last to be recruited. Since recruitment is planned to last approximately 6 months, this time period will cover approximately 9 months.

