#### Program costs

Program costs in addition to those for usual care will include those documented during the process evaluation, in particular: (1) training of the FECH nurse to implement the program; (2) the FECH nurse salary; (3) costs associated with providing discharge information to carers (costed on a case by case basis) – FECH nurse time and web access (to identify service providers), any costs for communication that is part of the intervention, and stationery used. Costs associated with research components/activities will be excluded since they would not be incurred if the program was taken up. Outcome costs associated with utilisation of health services during follow up for patients (cases and controls) will include: (1) cost of ED visits, (2) cost of additional in-patient hospitalisation, and (3) cost of ambulance use.

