In summary, this randomised controlled trial with embedded economic evaluation will determine carer, patient, and health service outcomes associated with introduction of a carer support program for carers of older patients being discharged from an acute medical unit in a tertiary hospital. The program may be appropriate for incorporation into routine post-discharge support if shown to be effective and if costs of implementation are offset by resultant cost savings.

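### Further testing is made conditional on no harm, but deaths are collected and not compared by arm, and service use cannot stand in for them

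*Protocol article*

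**What the plan says.** The final objective in the Background is to "Develop a plan for testing the FECH program in other health settings", and the condition attached to it is "should it be shown to have cost benefits and no negative patient/carer outcomes when implemented in the MAU".

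The patient hypothesis is that the program will "reduce (a) patients’ re-presentations and readmissions to hospital within 3 months of discharge", and will shorten stay when readmission occurs. Under Patient outcomes and data collection, the scope is "Quantitative patient outcome data will address Western Australian health care system utilisation". The same section names time at risk as one reason for obtaining death data and gives a second: "to capture deaths resulting from acute events during the study follow-up period, date and cause of death will be collected".

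Under Statistical analysis, Patient outcomes, total length of stay is compared by t-test (log-transformed if indicated). Numbers of readmissions and ED presentations are compared by the same method, with regression for confounders if relevant. Program costs says: "Outcome costs associated with utilisation of health services during follow up for patients (cases and controls) will include" three items, namely ED visits, in-patient stays and ambulance use. The economic Analysis section takes as its consequences the outcome measures already described for patients and carers.

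**The concern.** The condition asks whether patients came to harm, and the measures set for comparison ask how much hospital care they used. These can diverge in a population aged 70 and over, many of whom the article itself expects to be too unwell to approach.

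More readmissions or longer stays in the intervention arm would be visible as a negative patient outcome. Excess deaths need not be. A patient who dies at home soon after discharge contributes little or nothing to ED visits, bed days or cost. If such deaths were more frequent in the intervention arm, the service-use and cost comparisons could look neutral or favourable, and no stated between-arm comparison would contradict them. The trial holds the data that would reveal this but does not say it will use them for that purpose.

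**Working it through.** No figure in the plan is in dispute. The check sets the sections side by side, then sizes the mechanism and the precision available.

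**1. Where death appears**

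| Section | Content | Death compared by arm? |
|---|---|---|
| Background, hypotheses and objectives | Re-presentations, readmissions, length of stay | No |
| Patient outcomes and data collection | Service use; date and cause of death collected | Collected, no comparison stated |
| Statistical analysis, Patient outcomes | Totals by t-test or regression | No; time at risk not mentioned |
| Program costs | ED, in-patient, ambulance | No |
| Economic Analysis | Outcome measures already described | Not named |
| Sensitivity analysis table, effectiveness rows | Readmission, ED presentation, carer preparedness | No |
| Discussion | Death data named among the linked data | No analysis given |

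Carer-rated symptom and Barthel scores are collected at T1 to T3, but under Potentially confounding variables. They end at 6 weeks and cannot be obtained after death. The exit interviews are with intervention-arm dyads only.

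**2. Effect of excess deaths on raw counts**

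The document gives no mortality or readmission rates, so these are assumptions: the same event rate while alive in both arms, and deaths spread evenly over 90 days. Mean exposure is then 1 − p/2 for 90-day mortality p, and the ratio of expected counts is (1 − p_int/2)/(1 − p_ctl/2). If all deaths fell on day 0 the ratio would be (1 − p_int)/(1 − p_ctl).

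| Control vs intervention mortality | Even spread | All on day 0 |
|---|---|---|
| 5% vs 10% | 0.950/0.975 = 0.974 (−2.6%) | 0.90/0.95 = 0.947 (−5.3%) |
| 10% vs 20% | 0.900/0.950 = 0.947 (−5.3%) | 0.80/0.90 = 0.889 (−11.1%) |
| 5% vs 20% | 0.900/0.975 = 0.923 (−7.7%) | 0.80/0.95 = 0.842 (−15.8%) |

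With an assumed mean of 0.6 events per patient and even spread, the mean difference is 0.6 × (0.900 − 0.950) = −0.03 for 10% vs 20%, and 0.6 × (0.900 − 0.975) = −0.045 for 5% vs 20%. In a simulation of the planned t-test with 90 per arm, the chance of a falsely significant benefit rose from about 2.3% with equal mortality to about 4% and 5% respectively.

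**3. The direction can reverse**

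If each death is preceded by one extra admission, the difference in mortality is added: −0.03 + 0.10 = +0.07 for 10% vs 20%, and −0.045 + 0.15 = +0.105 for 5% vs 20%. The same excess mortality can push counts down or up.

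**4. Time at risk alone is not enough**

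Without terminal admissions, the simulated rate ratio per unit of person-time was about 1.00. An exposure term therefore removes the bias in the counts. A ratio of 1.00 alongside doubled mortality is also silent about the deaths.

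**5. Precision for a direct comparison**

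180 dyads give about 90 per arm. The 95% half-width is 1.96 × √(2p(1 − p)/90):

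- p = 0.05: 1.96 × √(0.095/90) = 0.064
- p = 0.10: 1.96 × √(0.180/90) = 0.088
- p = 0.15: 1.96 × √(0.255/90) = 0.104

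Power to detect 10% vs 20% at two-sided 0.05 is about 47%, and for 5% vs 10% about 25%. A non-significant result would be weak evidence of no harm.

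**The case against.** The strongest defence is that the authors have thought about death. They collect date and cause, state time at risk as a purpose, and mention death data again in the Discussion. The economic consequences could be read to take in everything under the patient data heading. The methods under Patient outcomes are partly given as examples, and a condensed article may leave a safety table to a fuller document. This shows that the data and some intention exist. It does not supply a comparison: the article lists the patient outcomes, analyses, costs and sensitivity variables, and death as a compared outcome is in none of those lists.

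Four stronger readings are tempting, and the documents do not support them.

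- A reader might take the condition as a rule for roll-out. It governs a plan for further testing. The objective nearest to adoption, "Refine the program from study recommendations and develop a plan to embed it into practice in the study setting and other similar health services", carries no such condition.
- A reader might see a contradiction with the closing statement that the program may suit routine use "if shown to be effective and if costs of implementation are offset by resultant cost savings". The two sentences concern different decisions, so they do not contradict each other.
- A reader might conclude that deaths always register as benefit. Step 3 shows that they can do the opposite.
- A reader might infer that p > 0.05 will be taken as proof of no harm. The article does not say how the condition will be judged.

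**Conclusion.** The point stands in limited form. The condition on further testing has no patient outcome set for comparison that can reveal a difference in mortality, although the necessary data are already requested. Time at risk is named at data collection and not carried into the described analysis. The resulting bias in the counts is uncertain in direction and modest: 2.6% to 7.7% with deaths spread evenly, and up to 15.8% in the extreme case of all deaths on day 0. These figures rest on assumed mortality and an equal event rate while alive. The main consequence is for what the trial can claim: as described, it could report no negative patient outcomes without having compared deaths. This is an inexpensive improvement worth making, and it does not undermine the primary carer outcome.

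**What to change.** 1. In Patient outcomes and data collection, and in the Patient outcomes analysis, add all-cause death within 3 months of index separation. Compare it by randomised arm as a risk difference with 95% CI, in all randomised dyads with linked data.
2. In the economic Analysis section, list death as its own row among the consequences, beside readmissions, ED presentations and cost.
3. Carry time at risk into the readmission, ED and length-of-stay comparisons.
4. In the last objective, base any statement about absence of negative outcomes on the reported 95% CIs for death and for the carer outcomes, and not on the lack of a significant difference.

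No new data are needed, because date and cause of death are already in the linkage request. The cost is one table row, an exposure term and some rewording. The downside is that an interval of about ±6 to ±10 percentage points will make the harm statement look less favourable.
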